## Abstract

**Background:**

Unpleasant experience with the previous menstruation can increase the sensitivity to pain which may lead to moderate to severe pain in patients with dysmenorrhea. Eye movement desensitization and reprocessing (EMDR) is a psychological method to alleviate the distress from unpleasant memories and related events and can be used for other conditions such as anxiety, depression, and chronic pain. This protocol was designed to investigate the effect of EMDR therapy on pain intensity in patients with dysmenorrhea.

**Methods/Design:**

A randomized clinical trial was designed in compliance with the Consolidated Standards of Reporting Trials (CONSORT). Female students who have moderate to severe primary dysmenorrhea (based on a visual analogue scale [VAS] score of at least 4 for two consecutive months) and who live in dormitories at Qazvin University of Medical Sciences in Qazvin, Iran will be invited to participate in the study. The total sample size will be 88 girls, who will be randomly assigned to intervention (*N* = 44) and control (N = 44) groups. EMDR therapy will be performed for the intervention group, while the control group can use sedative or other pain relife methods as their routin... There will be six treatment sessions, which will be held twice a week. The duration of each session is 30–90 min, according to the convenience of each participant. The data will be collected using the demographic characteristics questionnaire, the VAS, the Subjective Units of Anxiety or Distress Scale (SUD), and the Validity of Cognition Scale (VOC). The data on pain intensity due to primary dysmenorrhea in both groups will be collected at 1 and 2 months before the intervention (to identify eligible participants) and 1 and 2 months after the intervention (follow-ups). Data will be analyzed by using SPSS version 25 software and analysis of variance (ANOVA) with repeated measures with appropriate post hoc tests. A *P* value of less than 0.05 will be considered significant.

**Discussion:**

The results are expected to provide the information on the efficacy of EMDR therapy to manage moderate to severe pain in patients with primary dysmenorrhea.

**Ethics and dissemination:**

The research proposal is approved by the human ethics committee of Qazvin University of Medical Sciences (IR.QUMS.REC.1397.100). The results of this trial will be submitted for publication in a peer-reviewed research journal.

**Trial registration:**

IRCT20180823040851N1. Registered on 6, October 2018.

**Electronic supplementary material:**

The online version of this article (10.1186/s13063-019-3507-0) contains supplementary material, which is available to authorized users.

## Background

Primary dysmenorrhea or painful menstruation is the acute pelvic pain during menstruation [1] in the absence of any diagnosed pelvic disease, including endometriosis, pelvic inflammatory disease, and pelvic leiomyoma [2]. It is one of the most common disorders among women at reproductive age; reported prevalence ranges from 16% to 93% [3–6]. It is estimated that 3–40% of patients have experienced moderate to severe pain [4, 5, 7].

It is a major disruption of quality of life and significantly affects social activities among young women [8, 9]. In severe cases, dysmenorrhea can cause problems with performing daily routine activities and absence from school or the workplace [10]. About 1% of women are absent from work for 1 to 3 days each month because of severe dysmenorrhea, and about 14% of girls are absent from school each month because of menstrual cramps [11, 12]. Dysmenorrhea high costs to the health-care system [4].

It has been proposed that the pain severity of primary dysmenorrhea is determined by the increase in or unbalanced production of prostaglandins that cause uterine contractions, decrease uterine circulation, and increase the sensitivity of sensory nerves [13]. However, several other factors, including age, marital status, body mass index, familial history, and low socioeconomic status [2, 4, 8, 9, 14], can also affect the pain severity in patients with primary dysmenorrhea. In addition to the abovementioned factors, an association between certain psychological factors (including anxiety, depression, and stress) and the pain severity during dysmenorrhea has been found [15, 16]. Depression due to the impact of pain on social and occupational functions can not only reduce the response to medication but also enhance the perception of pain severity [11, 15]. Psychological distress and increased sensitivity to pain are well known to cause idiopathic pain disorders [17]. The role of pain sensitivity in patients with severe dysmenorrhea was proposed in a review by Iacovides et al. in 2015 [2]. In that review, the severity of dysmenorrhea not only was related to increased prostaglandin production but also increased sensitivity to pain in women with primary dysmenorrhea compared with healthy controls [2]. Painful menstruation, repeated on a monthly basis, can cause a central sensitivity to pain [18]. Central sensitivity is an abnormal pain mechanism in the central nervous system and can intensify the peripheral response to pain [19]. The relationship between depression, anxiety, and stress and dysmenorrhea can also be due to the association of these factors with the increased sensitivity to pain in women with dysmenorrhea [2]. On the other hand, it can be developed because of the emotional experience of menstrual pain since pain is not just a sensory experience but can be an emotional event affecting the development of psychological distress and emotional conditions, including mood disorders [20]. Epidemiological studies and clinical literature support the hypothesis that the repetition of uterine inflammation in menstrual cycles may increase the sensitivity to pain [21].

Despite various available therapies for the treatment of primary dysmenorrhea, the pain in some cases of primary dysmenorrhea remains uncontrolled [22] and this may be due to psychological factors. The latter can exacerbate pain and other problems caused by primary dysmenorrhea in young women and girls [23]. The prevalence of depression and anxiety in women with pelvic complaints suggests the involvement of psychological mechanisms in the development of menstrual pain in addition to the physiological mechanisms [24]. Given the potential role of psychological disturbances (such as previous unpleasant experiences with menstruation) and the significant correlation between primary dysmenorrhea and anxiety, stress, and depression, the effects of using psychological methods and behavioral interventions to manage this condition should be investigated [25].

Using psychological methods and behavioral interventions to manage physiological disorders is based on the theory that both psychological and environmental factors can impact on physiological processes. The purpose of these interventions is to modify an individual’s behaviors by increasing the awareness and adaptation of certain behavior but includes interventions for modifying thoughts or recognizing individuals and changing their behavior [25, 26]. The results from a systematic review showed positive outcomes of using behavioral interventions, including biofeedback, desensitization, and relaxation for pain relief in patients with dysmenorrhea [25].

Eye movement desensitization and reprocessing (EMDR) is one of the desensitization methods which does not rely on speech therapy or drug therapy but focuses on the regular and rapid movements of the eyes [27, 28]. It is a systematic, comprehensive, non-invasive, simple, and evidence-based treatment for unpleasant memories and related events [29]. EMDR therapy has been used to treat anxiety, depression, chronic pain, phantom limb pain, somatization syndrome, and post-traumatic stress disorder [30–35]. Various studies have shown a positive effect of EMDR therapy on eliminating physical and psychological symptoms caused by unpleasant life experiences [27]. Given that most studies using this method have been performed in patients with post-traumatic stress disorder, the efficacy of this method in treating other conditions still needs further investigation [36].

Primary dysmenorrhea has a chronic nature [37] which may lead to increased sensitivity to pain due to monthly recurrent uterine inflammation during menstrual cycles [21], trauma caused by the previous unpleasant experience with menstruation [38], and anxiety and depression associated with severe dysmenorrhea. Therefore, the present study was designed to investigate the effect of EMDR on pain intensity in patients with primary dysmenorrhea.

### Research aims and hypothesis

The hypothesis is that EMDR therapy can decrease the severity of pain or pain perception in patients with primary dysmenorrhea. The aims are to investigate the effects of EMDR therapy on the intensity of pain, distress level, and validity of cognition.

## Methods

### Design and setting

This is a randomized clinical trial. The study design is in compliance with the Consolidated Standards of Reporting Trials (CONSORT). Female students living in dormitories at Qazvin University of Medical Sciences in Qazvin, Iran are the study subjects. Figure 1 provides the CONSORT flow diagram. The protocol of this study is prepared based on Standard Protocol Items: Recommendations for Interventional Trials (Additional file 1).

**Fig. 1 Fig1:**
[figure not shown]
CONSORT (Consolidated Standards of Reporting Trials) flow diagram

### Participants

Single female students of reproductive age (18–35 years) who live in dormitories at Qazvin University of Medical Sciences and who experience moderate to severe dysmenorrhea in most menstrual cycles will be invited to participate in this study. Exclusion criteria are (1) secondary dysmenorrhea caused by endometriosis, adenomyosis, subacute endometritis, pelvic inflammatory diseases, ovarian cysts, or congenital anomalies of the pelvis and cervix; (2) history of psychological illnesses; (3) addiction to drugs; (4) history of seizure; (5) having strabismus and vision problems; (6) history of pelvic or abdominal surgery; (7) history of cardiovascular and pulmonary respiratory disease; and (8) graduation during the follow-up period.

After the preliminary screening, potential participants will be asked to evaluate their pain intensity for two consecutive months by using the visual analogue scale (VAS). Participants who report their dysmenorrhea as moderate to severe (VAS score of at least 4) for two consecutive months will be recruited for this study.

### Intervention

EMDR therapy will be performed in the intervention group. The participants are expected to attend all scheduled interventions in which the EMDR therapy will be implemented to manage their distressing memories of severe pain due to dysmenorrhea. The expected outcome is that the level of subjective distress will be reduced and positive cognition will be reorganized [27]. The EMDR therapy consists of eight essential phases, and several steps may be performed during one session:

Phase 1

This includes taking the history of the unpleasant condition, designing the treatment protocol, and preparing and evaluating the participant. This helps the therapist to determine the specific target to achieve. To identify this target, participants will be asked to talk about their memories of the menstruation, dysmenorrhea, and menstruation-related complaints as well as the epicenter of the pain. Then they will be asked to specify the traumatic event which disturbed them the most.

Phase 2: Preparation

Prior to initiation of the intervention for the first time, therapeutic targets should be established. The procedure of EMDR therapy and its effects and safety should be explained to the participants. Their questions and concerns should be addressed.

Phase 3: Assessment

In this phase, the components of the therapeutic target should be identified. When the memory has been identified, the participant will be asked to select the image that best stands for that memory. Then the participant will be asked to choose a negative cognition that expresses the dysfunctional self-assessment related to the unpleasant condition. In this phase, negative cognition about dysmenorrhea will be identified and the participant will be asked to imagine the worst picture about their dysmenorrhea. Then they will be asked to choose a positive cognition to be used to replace the negative cognition during the installation phase. They are encouraged to imagine having a less painful menstruation as a positive cognition.

Phase 4: Desensitization

This is the desensitization step that targets the thrilling feeling of the participant. In this phase, the participants will be asked to provide their pre-treatment Subjective Units of Anxiety or Distress Scale (SUD) and Validity of Cognition Scale (VOC) scores. Then eye movement sets will be used and the distressing memory of dysmenorrhea will be processed. At the end of the phase, the client reports their level of negative affect by using the SUD.

Phase 5: Installation

This phase focuses on cognitive rehabilitation and reconstruction and on strengthening the positive cognition to replace the negative cognition. In this phase, the researcher will try to install the positive cognition of menstruation without dysmenorrhea in the participant’s mind. The participants will be asked to provide their VOC scores.

Phase 6: Body scan

This phase assesses and evaluates the physical tensions. This step is also called the physical scan. After the positive cognition is installed, the participants will be asked to hold in their mind both the target event (dysmenorrhea) and the positive cognition (menstruation without dysmenorrhea) and then scan their own body mentally from top to bottom. Then they will be asked to identify any remaining discomfort in the form of body sensation.

Phase 7: Closure

The completion or final step consists of interactive reporting and is designed primarily to maintain the balance of the participant in the session and re-evaluate her at the end. In this phase, the participants will reach a state of emotional equilibrium. They will be informed of the possibility of having disturbing images, thoughts, or emotions between the sessions. This is a positive sign and they should not be concerned.

Phase 8: Re-evaluation

This is a reassessment step and its goal is to ensure that all relevant events have been processed [39, 40].

The EMDR therapy would be performed by one of the researchers (SV). She has been trained by a clinical psychotherapist to implement this type of therapy.

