### Measures

In this research, four instruments will be used for data collection:

*The demographic characteristics questionnaire* will be used to collect demographic and reproductive characteristics, including age, menarche age, education level, field of study, every menstrual cycle (length of menstrual period and bleeding period), and medication/drug use history. This questionnaire has been developed on the basis of the objectives of the study and its validity will be examined by the content validity method.

*The VAS* will be used to evaluate the severity of dysmenorrhea pain. An Iranian systematic review confirmed the validity and reliability of VAS for evaluation of dysmenorrheal pain [42]. The VAS is a 100-mm line where the “0” end (0) means completely painless and the other end (10) means the most intense pain imaginable. The patient marks the severity of pain on the line. The simplicity makes it easy to use for the assessment of pain [43].

*SUD* is a self-reporting scale with a 0- to 10-point rating scale. Participants are asked to report their level of distress or anxiety based on SUD scale. A score of 0 indicates the absence of distress, and a score of 10 indicates the maximum level of distress [39]. This scale has been widely used by Iranian researchers and its validity and reliability have been confirmed in their studies [44–46].

*The VOC* shows the level of belief in positive or negative recognition. Similar to the SUD scale, it is self-reporting and represents an individual’s assessment of her or his own cognition. A 7-point rating scale ranging from 1 to 7 is used to evaluate, quantify, and indicate the participant’s self-recognition. A score of 1 means a lack of belief in that particular cognition, and a score of 7 means a full belief in it [39]. This scale has been widely used by Iranian researchers and its validity and reliability have been confirmed in their studies [44–46].

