### Secondary outcome

The secondary outcomes are the need for pain relief during menstruation and potential side effects of EMDR therapy.

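### The closure phase labels foreseeable between-session disturbance as favourable, although EMDR side effects are a secondary outcome, so such events may go unreported or uncounted

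*Protocol article*

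**What the plan says.** The Intervention section of the protocol article, Phase 7 (Closure), says of women in the EMDR arm: "They will be informed of the possibility of having disturbing images, thoughts, or emotions between the sessions". The next sentence is "This is a positive sign and they should not be concerned".

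The Secondary outcome section lists "potential side effects of EMDR therapy" among the outcomes. The Discussion expects the results to inform on safety as well as efficacy.

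On roles, the Intervention section states: "The EMDR therapy would be performed by one of the researchers". The initials given there are the same as those of the person whom the Data management section makes responsible for collecting the data. The Blinding section rules out blinding of participants and researchers.

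The text also gives women openings to speak. In Phase 2, "Their questions and concerns should be addressed". Of Phase 7 itself it says: "The completion or final step consists of interactive reporting".

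**The concern.** The between-session disturbance named in Phase 7 is the one unwelcome psychological effect that the article itself foresees. It is also a natural candidate for the side-effect outcome. Labelling it in advance as good news and no cause for worry pulls against measuring it as a possible harm.

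If the label has an effect, the recorded side-effect rate would be too low in a trial that is meant to say something about safety. A woman with marked or lasting distress might also wait before mentioning it. The outcome is secondary and concerns the treated arm only; the comparison of pain between the arms does not depend on it.

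**Working it through.** There is no figure in the plan to reproduce. The check sets the stated provisions side by side.

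1. **Who could be influenced.** The article does not make clear whether the favourable label is said to participants or is the authors' own comment.
   - If it is said to participants, they have less reason to mention the experience.
   - If it is a comment, it still tells the therapist to regard the experience as favourable. By the initials, that therapist has the general data-collection role and is unblinded.

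   A route to under-recording exists on either reading.

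2. **Whether other stated measures would catch the events.**
   - Measures section: "In this research, four instruments will be used for data collection". These are the demographic questionnaire, VAS, SUD and VOC, and none is described as asking about experiences between sessions.
   - SUD in Phase 4: one rating is taken before the eye movements. Of the later one the text says: "At the end of the phase, the client reports their level of negative affect by using the SUD". The later rating follows work on the dysmenorrhea memory within the session. The earlier one, if repeated at later sessions (the text leaves this open), could reflect marked distress carried over. It would not identify the source.
   - Phase 8 revisits the participant, but its stated goal is complete processing, which is therapeutic.
   - Treatment fidelity section: a clinical psychotherapist monitors the therapist, and 15% of sessions are rated. This checks delivery of the therapy, not side effects.

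   Each is at best a partial check, and none is a safety record.

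3. **Whether the follow-ups would catch them.** The Number of intervention sessions section sets six sessions at two per week. Study procedure places the follow-ups, described there as evaluating pain, at 1 and 2 months after the last session. Assume all six sessions are held, even spacing (7 / 2 = 3.5 days) and a month of 30 days:
   - first to last session: 5 x 3.5 = 17.5 days;
   - last session to first follow-up: 30 days;
   - first session to first follow-up: 30 + 17.5 = 47.5 days.

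   The between-session experiences would lie about 30 to 48 days back, so asking during treatment is the better occasion.

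4. **Size.** With 44 women in the EMDR arm, let p be the share with at least one such experience and u the share of those left unrecorded. Women missed = 44 x p x u, and the recorded share is p x (1 - u). The document gives neither p nor u, and u may be zero. No estimate is possible.

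**The case against.** The strongest reply is that no provision contradicts another. Phase 7 describes part of the therapy and the outcome section names an outcome. An expected, forewarned event can still be recorded as a side effect, and forewarning may even prompt women to mention it. The full protocol may hold a routine side-effect question, which a condensed article would commonly leave out.

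Much of this stands. A reader might infer that participants are told to keep such experiences to themselves; the text says no such thing. A reader might infer that the therapist is the named collector of side-effect data; Data management gives only a general role. A reader might also take the lack of a side-effect form as the fault; in a condensed article it is not one.

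What remains is the stated label. A form elsewhere would reduce its effect but not remove it, because the women answering and the person recording would still have been told that these experiences are a good thing.

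A second reply concerns the remedy. Distress is a primary outcome, and repeated questions about disturbing thoughts in the EMDR arm alone could influence SUD. This stands, and it limits when the question should be asked.

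**Conclusion.** The point holds in a modest form. The stated label sits badly with the stated safety outcome, and under-reporting or under-counting is plausible. It rests on an inference about how participants or the recorder respond to the label, and on shared initials for the overlap of roles. The document does not support the stronger conclusion that EMDR will look safer than it is: the size is unknown and nil is possible. Importance is low and confined to the side-effect outcome and participant welfare; pain results and sample size are untouched.

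**What to change.** - Keep the forewarning in Phase 7, but drop the favourable label or balance it.
- Ask participants to tell the team about any such experience, and promptly if it is marked or persistent.
- State in the outcome definition that these experiences count as potential side effects whether or not they are seen as therapeutic. This takes the classification out of the therapist's discretion.
- Ask one brief neutral question at the start of each session after the first, once any SUD and VOC ratings due at that point have been given, so that it cannot influence them. Do not add an EMDR-only question at the follow-ups, where it could affect later ratings in one arm.
- Report the answers descriptively for the EMDR arm.

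**Cost.** A few sentences of text and a few seconds per session. Each woman is asked at most 6 - 1 = 5 times: 5 x 44 = 220 answers, or 5 x 41 = 205 if only the 41 per arm required before the dropout allowance remain. Women who reach the target early give fewer. Ratings later in the same session still follow the question, so it should be kept short and neutral. The reported side-effect rate may look less favourable. According to the Trial status section recruitment has not begun, so the change can be made before anyone is treated.
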